## Materials and methods

### Study design

This single-center randomized clinical trial will be performed at the Laboratory of Physical Activity and Health Promotion (LABSAU) at the University of Rio de Janeiro State (RJ, Brazil), where a supervised exercise program particularly designed for PLHIV is held since 2005. PLHIV will be recruited in the outpatient clinic of the University hospital, and uninfected volunteers matched for age, sex and body mass will be randomly recruited from the staff of the same institution to compose a reference group. All subjects will receive oral and written instructions about the study risks and benefits and will be included in the study only after giving written informed consent. Recruitment, pre-participation screening and data collection will occur between February 2022 and December 2023. We believe that results will be available for analysis in 2024.

The trial was registered at ClinicalTrials.gov (registration number: NCT04512456, date of registration: August 13, 2020) and approved by the Ethics Committee of the Pedro Ernesto University Hospital (approval number 41955620.2.0000.5259, opinion number 4.520.721, approved in February 2, 2021). The study complies with the SPIRIT 2013 recommendations (Standard Protocol Items: Recommendations for International Trials) (supporting information) [25]. The Fig 1 depicts the overall schedule and time commitment for trial participants [25].

**Fig 1 pone.0265516.g001:**
[figure not shown]
Schedule of enrolment, interventions, and assessments. -*t*_1_, enrolment week 0; *t*_0_, allocation and baseline week; *t*_3_, post-intervention (week 12).

### Participants and recruitment

Eligible PLHIV will be men and women aged 30- to 50 years, diagnosed with HIV/AIDS [26], but asymptomatic and free from opportunist infections. Exclusion criteria will be: a) use of cART for less than 3 years; b) regular physical exercise (≥ 3 days/week during 30 min) in the last 6 months; c) current or past diagnosis of hypertension, coronary artery disease, ischemic disease, pulmonary disease, diabetes mellitus, Chagas disease, tuberculosis, or heart failure; d) malnutrition; e) use of antidepressant or antihypertensive medication, and f) smoking habit. Uninfected controls will be screened for items b, c, d, e, and f.

Forty-two PLHIV will be randomized through a random code generator software (www.randomization.com) at a ratio of 1:1 into intervention or control groups. Therefore, the experiment will have three groups: a) PLHIV under training (PLHIV-T; n = 21), which will enroll in the multimodal exercise training during 12 weeks; b) PLHIV controls (PLHIV-C; n = 21), which will remain in clinical care and shall not to change their physical activity behavior; c) Uninfected controls (CONT; n = 21), which shall not change their physical activity behavior. For ethical reasons, the PLHIV-C group will have the possibility to undertake the exercise training intervention once the trial ends. Outcomes in PLHIV-T and PLHIV-C will be assessed before randomization at baseline and after intervention, whereas in CONT only at baseline to provide reference values. The study flowchart is presented in Fig 2.

**Fig 2 pone.0265516.g002:**
[figure not shown]
Study flowchart.

### Experimental design

Assessments will be undertaken in a single visit, as shown in Fig 3. All procedures will take place at the same time of the day (9–11 am) to minimize circadian effects, in a quiet temperature-controlled environment (21–23°C). Participants will be instructed to fast for 2 h, to avoid physical exercises in the 48 h, and caffeine or alcohol in the 12 h prior to experimental sessions.

**Fig 3 pone.0265516.g003:**
[figure not shown]
Experimental design.

After a general medical examination and anthropometric measurements, participants will remain 30 min at rest in a supine position before performing a mental stress task and handgrip strength test. The mental stress task will provide information about the integrity of pathways of stress-induced sympathetic responses mediated by the central command. Maximal voluntary contraction (MVC) assessed by the handgrip test will be used to determine the loads applied during the metaboreflex activation protocol, and to detect possible strength differences between groups at baseline and after intervention. Subsequently, the muscle metaboreflex will be activated using a post-exercise circulatory arrest (PECA) protocol, during which blood lactate will be assessed. Then, a capsaicin-based analgesic balm (0.1%, FarmaSite, Itaúna, Brazil) will be applied over the exercising arm to stimulate the metabolically sensitive muscle afferents via TRPv1 receptors [27], and after 30 min of topical application, PECA will be repeated.

Primary outcomes will be BP and heart rate variability (HRV) indices reflecting autonomic modulation. Secondary outcomes will be the heart rate (HR), peripheral vascular resistance (PVR), stroke volume (SV), cardiac output (CO), blood lactate concentration, anthropometric markers, and handgrip MVC.

### Intervention

Patients included in the intervention arm will participate of an exercise training program during 12 weeks, consisting of 60-min sessions performed 3 days/week and including aerobic, resistance, and flexibility exercises, as described elsewhere [28]. Treadmill or cycle ergometer aerobic exercise will last 30 min with an intensity range corresponding to 50–80% of the heart rate reserve. Resistance training will consist of 20 min of exercises for the major muscle groups of the upper and lower limbs (8–10 single and multi-joint exercises with free weights and machines), performed with 2–3 sets of 10–12 maximum repetitions (RM) and load corresponding to 80–90% of 10 RM. At the end of the sessions, the participants will perform a 10-min static stretching routine involving major joints (2 sets of 6- to 8 exercises, holding the maximal range of motion for 30-s) [28–30].

Heart rate will be monitored to ensure proper aerobic exercise intensity (Polar H10; Polar Electro^TM^, Kempele, Finland). All training sessions will be performed indoors (21–23°C), always in the morning and under the supervision of the research staff. The participants will be instructed on the importance of clinical follow-up and the benefits of regular physical activity to improve adherence to intervention.

### Mental stress test

To investigate the integrity of muscle metaboreflex efferent pathways, a mental stress assessment will be performed using the Stroop Color-Word test [31], which has been widely used for stress-induced sympathetic effects mediated by the central command, regardless of the muscle metaboreflex activation [32]. The test will be administered for 5 min by a single researcher that will display slides changing every 2 s, showing color names written in different colors. The volunteers will identify the word colors irrespective of the written information. Changes from rest in autonomic and cardiovascular outcomes will be recorded as outcomes.

### Muscle metaboreflex activity assessment

Muscle metaboreflex will be activated by a PECA protocol, which has been shown to trap muscle metabolites in the exercising limb and to maintain stimulation of group IV muscle afferents without the activity of the central command and mechanoreflex [12]. PECA will consist of 13 min, as follows: 5 min of rest, 2 min of isometric handgrip exercise with the dominant arm with a load corresponding to 40% of MVC, 3 min of vascular occlusion, followed by 3 min of recovery. Vascular occlusion will be applied in the exercised limb by inflating a cuff at 240 mmHg 5 s before the end of exercise, and then deflating it in the 3-min recovery. During PECA, the volunteers will be in a sitting position, and shall avoid performing the Valsalva maneuver and any movement, except for the handgrip. Changes from rest during PECA will be calculated for autonomic and cardiovascular outcomes.

Prior to PECA, a brief familiarization with the handgrip exercise will be allowed. Handgrip force exerted will be placed in front of the subjects to guide the contraction intensity. Vascular occlusion in PECA will be applied using a nylon cuff size 11 x 85 cm connected to a pneumatic cuff inflator Hokanson TD312 (D. E. Hokanson^TM^ Inc, Bellevue, Washington, USA) placed around the proximal third of the dominant arm. A vascular Doppler probe (DV 610B Medmega Industria de Equipamentos Medicos, Franca, SP, Brazil) will be placed over the brachial artery (dominant arm) to capture the auscultatory pulse and confirm the vascular occlusion during the PECA protocol. The Fig 4 details the PECA protocol.

**Fig 4 pone.0265516.g004:**

Post-exercise circulatory arrest (PECA) protocol used during muscle metaboreflex activity assessment.

### Primary outcomes

#### Blood pressure

Systolic and diastolic BP will be assessed in the non-dominant arm using a digital sphygmomanometer (Omron HEM—7113, Kyoto, Japan) positioned around the proximal third of the non-dominant arm. Data will be assessed at rest, and every minute during mental stress and muscle metaboreflex assessments.

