### Secondary outcomes

#### Hemodynamic parameters

BP and HR will be continuously and non-invasively measured on a beat-to-beat basis using finger photoplethysmography (Finometer PRO, Finapres, Enschede, Netherlands). For this, an appropriate size cuff will be placed around the middle finger of the non-dominant hand, which will be supported on a table and positioned at the heart level. BP waveform measured at middle finger will be calibrated for each participant using an automatic cuff placed around ipsilateral arm [36]. SV will be estimated from finger pressure waveform using Modelflow method (BeatScope 2.1, Finometer PRO, Finapres, Enschede, Netherlands) [37]. CO will be obtained multiplying HR by SV, and PVR will be the ratio of mean BP to CO. Brachial BP measured with the digital sphygmomanometer will be used to validate Finometer measurements of absolute blood pressure.

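### The every-minute upper-arm cuff and the continuous finger pressure recording share the non-dominant limb, so the waveform behind stroke volume, cardiac output and vascular resistance is interrupted during mental stress and PECA

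*Protocol article*

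**What the plan says.** All references are to the Protocol article.

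- **Primary blood pressure** (Blood pressure, under Primary outcomes). The digital sphygmomanometer is "positioned around the proximal third of the non-dominant arm". On timing: "Data will be assessed at rest, and every minute during mental stress and muscle metaboreflex assessments".
- **Finger recording** (Hemodynamic parameters, under Secondary outcomes). "BP and HR will be continuously and non-invasively measured on a beat-to-beat basis using finger photoplethysmography". For this, "an appropriate size cuff will be placed around the middle finger of the non-dominant hand". The waveform is "calibrated for each participant using an automatic cuff placed around ipsilateral arm". The sphygmomanometer readings also serve as the check on the finger device's absolute pressure.
- **Derived outcomes** (same section). "SV will be estimated from finger pressure waveform using Modelflow method", and "CO will be obtained multiplying HR by SV, and PVR will be the ratio of mean BP to CO".
- **The other arm** (Muscle metaboreflex activity assessment). The dominant arm performs the handgrip and carries the 240 mmHg occlusion cuff. The same section calculates change from rest during PECA for the cardiovascular outcomes.

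**The concern.** Arm, site and frequency are all fixed in the text, and they conflict. A pressure waveform taken at the finger cannot be continuous while a cuff upstream on the same arm is inflated once a minute. Neither device can simply move to the dominant arm during PECA, because that arm is exercising and then occluded.

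The outcomes at stake are SV, CO, PVR and finger blood pressure. They are secondary, but the Discussion relies on the hemodynamic measures, together with lactate and the TRPv1 manipulation, to explain any training effect on the metaboreflex. The occlusion minutes are the ones meant to isolate that reflex, and they are among the minutes interrupted. The problem recurs in PECA without and with the capsaicin balm, and at both visits of the randomized groups.

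The article also does not say how often the cuff is read at rest. If it is read less often there than during the tests, change from rest would set a largely clean baseline against a heavily interrupted stage.

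**Working it through.** There is no stated figure to reproduce, because the point concerns device placement. The check has two parts.

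**1. Can the instructions be carried out together?**

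| Item | Limb | Timing | Section |
|---|---|---|---|
| Sphygmomanometer cuff | Non-dominant upper arm | At rest, then each minute of the tests | Blood pressure |
| Finger pressure cuff | Non-dominant middle finger | Beat to beat, continuous | Hemodynamic parameters |
| Calibration cuff for the finger device | Same side as the finger cuff | Not stated | Hemodynamic parameters |
| Handgrip and occlusion cuff | Dominant arm | Handgrip 2 min, then occlusion 3 min | Muscle metaboreflex activity assessment |

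The first two rows use the same limb in the same minutes. No visible text alternates arms, staggers the recordings or excludes affected beats. It is also not stated whether the calibration cuff and the sphygmomanometer are one device. If they are two, both occupy one upper arm.

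**2. How much signal is affected?**

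Inputs from the article: one reading per minute; Stroop test 5 min; handgrip 2 min; occlusion 3 min. The disturbance per reading, *t*, runs from inflation until the finger pulse has recovered. The article gives no value, so *t* is assumed to lie between 20 and 50 s.

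- Share of each minute affected = *t* / 60
- Clean signal in a stage = minutes × (60 − *t*) seconds

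| Assumed *t* | Share affected | Occlusion: 3 × (60 − *t*) | Handgrip: 2 × (60 − *t*) | Stroop: 5 × (60 − *t*) |
|---|---|---|---|---|
| 20 s | 20/60 = 33% | 120 s | 80 s | 200 s |
| 30 s | 30/60 = 50% | 90 s | 60 s | 150 s |
| 40 s | 40/60 = 67% | 60 s | 40 s | 100 s |
| 50 s | 50/60 = 83% | 30 s | 20 s | 50 s |

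**Which outcomes depend on this signal.** SV is estimated from the finger waveform. CO is HR times SV, and PVR divides mean pressure by CO, so a disturbed SV carries into both. Finger blood pressure is affected directly. Cuff pressure is measured by the device causing the interruption and is not lost. Heart rate variability, and a beat-to-beat heart rate, come from a separate heart rate monitor (Heart rate variability indices).

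**The case against.** **Operating detail and missing figures.** A journal article usually leaves the timing of readings within a minute and the handling of artefact beats to the full protocol. Fig 4, which is said to detail PECA, was not available for this review. This stands in part: the absence of an exclusion rule is not in itself a fault. The same-arm, every-minute placement is stated outright, however, and a figure giving timings would not remove it.

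**Enough signal may remain.** At an assumed 70 beats per minute, 30 to 120 s of clean occlusion signal is 30 × 70/60 = 35 to 120 × 70/60 = 140 beats, which may be adequate for a stage mean. This also stands, but only if the clean beats are separated from the rest. As written, disturbed beats go into the average.

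**Stronger readings that the document does not support:**

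- *The primary blood pressure outcome is compromised, or too noisy because occlusion allows only about three cuff readings.* The cuff readings survive the conflict. The article gives no measurement error for either device, and the blood pressure method behind the planning standard deviation of 4.6 mmHg is not described. It therefore cannot be shown that the readings are more variable than planned. Setting the 3.5 mmHg target against three readings also compares a group difference with a count per person.
- *Primary blood pressure should move to the finger device.* The Abstract and the Blood pressure section name the sphygmomanometer, and the article uses it as the reference for absolute pressure. Replacing it would change the measurement of a primary outcome, and this conflict does not require that. Cutting the cuff to one reading per stage would give up primary data to protect secondary outcomes.
- *The comparison between trained and control participants is biased.* Both randomized groups follow the same procedure, and nothing in the text suggests that the disturbance differs between them.

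**Conclusion.** The conflict holds for the finger-derived secondary outcomes only. The two measurement sections assign overlapping recordings to one limb, and following both would interrupt the finger waveform about once a minute during mental stress and PECA. Between a third and five sixths of each minute would be affected, leaving 30 to 120 s of the 3-min occlusion.

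This rests on two things the article does not state: that inflating the upper-arm cuff above systolic pressure stops the finger pulse, which is a physical inference, and that each reading disturbs the signal for 20 to 50 s, which is an assumption. The first is hard to dispute. The second sets the size but not the existence of the problem.

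The consequence is a weaker mechanistic account from SV, CO and PVR, and a compromised device check, since finger pressure cannot be read on that arm while the cuff is inflated. The point is worth correcting because the remedy is cheap, but it does not threaten the primary analysis.

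**What to change.** Reconcile the Blood pressure and Hemodynamic parameters sections as follows.

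1. Keep the upper-arm cuff as the primary blood pressure device, and fix the second within each minute at which every reading starts.
2. Compute SV, CO, PVR and finger blood pressure as stage means using only beats outside the period from the start of inflation until a pre-set time after deflation.
3. Apply the same windows at rest, in both PECA runs and at both visits, so that each change from rest compares like with like.
4. Compare the finger device with the cuff using the finger beats just before each inflation.
5. Replace the description of the finger recording as continuous with one that states these gaps, and say whether the calibration cuff is the same device as the sphygmomanometer.

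The cost is fewer usable beats per stage for the secondary outcomes: if the disturbance were as long as 50 s, only 10 s per minute would remain. Timing the cycle on the actual device before setting the exclusion period would show where in the range the trial lies. No new equipment is needed and the primary outcome definition does not change. For recordings already made, the exclusion rule can still be applied if inflation times can be identified, but the lost beats cannot be recovered.

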#### Heart rate variability indices

The HRV indices reflect cardiac autonomic modulation. Beat-to-beat HR will be continuously recorded using a heart rate monitor (Polar V800; Polar^TM^ Electro, Kempele, Finland) [33] at rest, during the mental stress task, and muscle metaboreflex activation protocol. The signals will be transferred to the Polar Precision Performance Software (Polar Electro, Kempele, Finland). After replacing the non-sinus beat by interpolated data derived from adjacent normal RR intervals, times series data will be exported to Kubios^TM^ HRV program for analysis (Version 3.4, University of Kuopio, Kuopio, Finland).

Time domain variables will be: mean normal RR intervals (RRi), standard deviation of normal NN intervals (SDNN), square root of the mean squared successive differences from adjacent RRi (rMSSD), and percentage number of pairs of adjacent RRi differing by more than 50 ms from previous RRi (pNN50). SDNN, rMSSD, and pNN50 are acknowledged to reflect the parasympathetic modulation within short periods [34]. Spectral analysis will be performed by the Fast Fourier transform method, with frequency bands corresponding to low-frequency (LF: 0.04–0.15 Hz), high-frequency (HF: 0.15–0.40 Hz), and total power (TP; meaning LF plus HF) [35]. The LF and HF reflect a predominance of combined sympathetic-parasympathetic and isolated parasympathetic modulation, respectively [35], while LF: HF ratio will be adopted as a marker of sympathovagal balance.

### Secondary outcomes

#### Hemodynamic parameters

BP and HR will be continuously and non-invasively measured on a beat-to-beat basis using finger photoplethysmography (Finometer PRO, Finapres, Enschede, Netherlands). For this, an appropriate size cuff will be placed around the middle finger of the non-dominant hand, which will be supported on a table and positioned at the heart level. BP waveform measured at middle finger will be calibrated for each participant using an automatic cuff placed around ipsilateral arm [36]. SV will be estimated from finger pressure waveform using Modelflow method (BeatScope 2.1, Finometer PRO, Finapres, Enschede, Netherlands) [37]. CO will be obtained multiplying HR by SV, and PVR will be the ratio of mean BP to CO. Brachial BP measured with the digital sphygmomanometer will be used to validate Finometer measurements of absolute blood pressure.

#### Blood lactate concentration

Blood lactate will be measured to verify the metabolic stress induced by PECA. With this purpose, the fingertip of the exercising arm will be punctured with an automatic lancet and 25 μl of capillary blood sample will be collected during PECA, at minutes 5, 7 and 10. The blood sample will be transferred to a microtube containing 50 μl of 1% sodium fluoride, and blood lactate concentration will be determined by the YSL 2700 analyzer (Yellow Spring^TM^ Co., Yellow Springs, Ohio, USA).

#### Anthropometry

Height and body mass will be assessed by a digital scale (Filizola^TM^, Sao Paulo, SP, Brazil), and wall-mounted stadiometer (Sanny^TM^, Sao Paulo, SP, Brazil), respectively. The BMI will be calculated (Kg/m^2^).

#### Handgrip maximal strength test

Handgrip MVC will be assessed using a hydraulic handgrip dynamometer (Saehan, SH5001, Holliston, MA, USA). Strength measurements will be performed with participants in a sitting position, arm along the body, and elbow in flexion (dominant arm). The volunteers will make three attempts of 5 s interspersed with 2-min intervals, and the highest value will be recorded as result.

### Sample size calculation and statistical analysis

Sample size was calculated using GPower 3.1.9.4 (Universität Kiel, Kiel, Germany) to detect longitudinal differences between groups in systolic BP response due to metaboreflex gain. Considering a between-group difference of 3.5 mmHg (standard deviation of 4.6 mmHg) [23], 80% power and 5% significance level, and increasing the sample size by 50% to account for losses to follow up, a total of 21 participants in each group was calculated as necessary.

Descriptive analysis will consist of mean and standard deviation for continuous variables and percentage for categorical variables. Data normality will be checked by the Shapiro Wilk test, and data will be presented as mean and standard deviation or percentage, whenever appropriate. A cross-sectional comparison between PLHIV-T, PLHIV-C and CONT will be performed at baseline by means of one-way ANOVA (continuous) or chi-squared test (categorical).

Longitudinal effects of exercise training on primary and secondary outcomes will be evaluated through linear mixed models (LMM) including treatment (PLHIV-T or PLHIV-C) and time as fixed effects, and group *vs*. time interaction. LMM, which correlates with repeated measures over the time, allows an intention-to-treat analysis as it includes all observations of each one of the participants, regardless of losses to follow-up or noncompliance to exercise protocol. Residual plots of all models will be examined and the likelihood-ratio test will be used to compare and select random intercept or random slope models. Data analysis will be performed using Stata 13.0 (StataCorp, College Station, TX, USA), and in all cases the statistical significance will be set at *P* ≤ 0.05.

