Exercise training seems to improve sympathetic activity control and/or abnormal cardiovascular responses to muscle metaboreflex activation in several chronic conditions [17–20]. Although very little information is available on the potential mechanisms by which exercise training favors the muscle metaboreflex, they seem to include a wide spectrum of adaptations, as increased muscle perfusion with lower metabolite accumulation, greater antioxidant capacity, and changes in the expression of receptors evoking metaboreflex (i.e., the transient receptor potential vanilloid receptor 1 –TRPv1) [21]. Individuals with impaired metaboreflex have deficiencies in one or more of those mechanisms, and therefore might be more responsive to exercise training than healthy individuals [21]. This is the case of PLHIV, who often present lactic acidosis [22] and attenuated pressor response to metaboreceptor stimulation [23].

Despite this, we could not find research investigating muscle metaboreflex adaptations and its underlying mechanisms to exercise training in PLHIV. This would be nonetheless useful to determine the potential impact of exercise training on mechanisms controlling autonomic modulation during exercise, which have prognostic value [24]. Thus, the aim of the present study is to describe the experimental protocol of a randomized controlled trial designed to investigate the effects of a multimodal supervised exercise program (i.e., aerobic, resistance and flexibility exercises) on hemodynamic and autonomic responses to muscle metaboreflex activation in PLHIV. In addition, potential mechanisms of exercise training adaptations in the muscle metaboreflex will be analyzed by assessing blood lactate concentration and activating TRPv1. We will test the hypothesis that a multimodal exercise training would be able to increase the neurocardiovascular responses during metaboreflex activation by reducing blood lactate levels at rest and increasing TRPv1 sensitivity.

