## Discussion

The findings of the present study may help to elucidate the role of exercise training to produce adaptations in autonomic and hemodynamic responses induced by muscle metaboreflex in PLHIV. Prior research has demonstrated that PLHIV present abnormal pressor response during muscle metaboreceptor stimulation [23] and autonomic dysfunction at rest [38] and after exercise [9]. When group IV muscle afferent feedback is impaired, the increase in BP may not be enough to assure an appropriate muscle blood flow and oxygen supply, leading to premature fatigue and exercise intolerance [16], as previously reported in PLHIV [39].

Most studies addressing the effects of exercise training in PLHIV have focused on physical fitness, body composition, immune function, mental health or lipid profile [40–42], whereas the neurocardiovascular function of these patients has gained little attention. To the best of our knowledge, there are only two clinical trials investigating the role of exercise training on the autonomic function in PLHIV [43, 44]. Quiles et al. [43] have recently demonstrated that an 8-week aerobic exercise program improved the overall autonomic function of these patients, while Pedro et al. [44] did not observe changes in HRV after 16 weeks of concurrent training. Additionally, we could not locate studies investigating the role of exercise training on the muscle metaboreflex among these patients.

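### The 3.5 mmHg difference and 4.6 mmHg SD used to size the training comparison come from a study cited only for impairment in PLHIV, so the article gives no basis for either as a training effect or as the SD of a change

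*Protocol article*

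**What the plan says.** In the protocol article, the section on sample size and statistical analysis gives the purpose of the calculation as "to detect longitudinal differences between groups in systolic BP response due to metaboreflex gain". The inputs are "Considering a between-group difference of 3.5 mmHg (standard deviation of 4.6 mmHg) [23], 80% power and 5% significance level". The result is then raised for attrition ("increasing the sample size by 50% to account for losses to follow up"), and the section concludes that "a total of 21 participants in each group was calculated as necessary". Randomisation of the 42 PLHIV is "at a ratio of 1:1 into intervention or control groups" (Participants and recruitment), so the contrast being sized is trained PLHIV against untrained PLHIV, tested by the group-by-time interaction of a linear mixed model.

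The article uses reference 23 in two other places. The Introduction cites it for an "attenuated pressor response to metaboreceptor stimulation [23"] in PLHIV, and the Discussion cites it for an abnormal pressor response in the same population. On training, the Discussion says that "we could not locate studies investigating the role of exercise training on the muscle metaboreflex among these patients", and the Introduction says the same in other words.

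**The concern.** A planning difference for a training trial can rest on training data or on a stated smallest difference worth detecting. Here it rests on a reference that the article otherwise describes as evidence of impairment. By the authors' own account of the literature, that reference cannot be a comparison of trained and untrained PLHIV. No sentence argues that 12 weeks of training would produce 3.5 mmHg or that 3.5 mmHg is the smallest change of interest.

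The SD has the same weakness. The planned test concerns the change in the pressor response between baseline and week 12, and the SD of that change depends on a pre-post correlation that the article does not give. A figure of 4.6 mmHg from a study of impairment may be the spread of the response at one visit.

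At stake is what the stated power means. A reader will take 80% as the chance of finding a realistic training effect, and the article does not support that reading.

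**Working it through.** **Inputs.** From the sample-size section: difference 3.5 mmHg, SD 4.6 mmHg, power 80%, significance level 5%, increase of 50% for losses, 21 per group. Sidedness is not stated; two-sided is assumed. The 21 per group implies 21 / 1.5 = 14 completers per arm if all the planned losses occur.

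**Step 1: the plan's own figure.** Standardised difference d = 3.5 / 4.6 = 0.761.

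- Normal approximation: n per arm = 2 × (1.96 + 0.84)² / d² ≈ 27.1, rounded up to 28. The exact t-test needs 29.
- Times 1.5: 42 or 44 per arm, against the stated 21.

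The stated 21 is not reproduced by a two-group comparison on these inputs. Since 28 × 1.5 = 42 equals the two-arm total, a per-arm number may have been read as a total. About 21 is otherwise reached only under choices that the article does not state, such as a one-sided paired test (13 × 1.5, rounded up to 20) or a high pre-post correlation. That is a separate defect. It matters here because it sets the power at the planned size.

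**Step 2: power and detectable difference at the planned size.** Two-sided t-test with 2n − 2 degrees of freedom, noncentrality d × √(n/2), SD 4.6. The detectable standardised difference at 80% power is 0.886 for n = 21 and 1.100 for n = 14.

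| | 21 per arm | 14 completers per arm |
|---|---|---|
| Detectable difference | 0.886 × 4.6 = 4.1 mmHg | 1.100 × 4.6 = 5.1 mmHg |
| Power at 3.5 mmHg | 67% | 49% |
| Power at 2.625 mmHg (75% of 3.5) | 44% | 31% |
| Power at 1.75 mmHg (50% of 3.5) | 23% | 16% |

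**Step 3: if 4.6 is a single-visit SD.** The SD of a change is then 4.6 × √(2(1 − ρ)), where ρ is the pre-post correlation. The documents give no ρ; the values below are assumptions. All results are for 21 per arm.

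| Assumed ρ | SD of change | Detectable difference | Power at 3.5 mmHg | Power at 1.75 mmHg |
|---|---|---|---|---|
| 0.3 | 5.44 | 4.8 mmHg | 53% | 17% |
| 0.5 | 4.60 | 4.1 mmHg | 67% | 23% |
| 0.7 | 3.56 | 3.2 mmHg | 87% | 34% |

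The stated 80% can thus be too high or too low, depending on a quantity that the article leaves open.

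**Step 4: what remains if the arithmetic is corrected.** At 29 completers per arm with SD 4.6, the detectable difference is 3.4 mmHg and power at 3.5 mmHg is 81%. The question of why 3.5 mmHg is the right target for a training contrast is unchanged.

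**The case against.** The strongest defence is that a planning difference may be a target rather than a forecast. The section speaks of detecting a difference and does not predict one. Lack of training data in PLHIV is the reason for the trial, and any trial sized for one difference has low power at half of it. All of this stands. The low power at 1.75 mmHg does not show that the source is wrong. But the article does not present 3.5 mmHg as a target; it attaches a citation that does not address the contrast.

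It is also fair that detectable differences above 3.5 mmHg at 21 per arm with SD 4.6 reflect the arithmetic defect, not the choice of source, and that the mixed model could do better than the t-test if the pre-post correlation is high. Step 3 shows this for ρ = 0.7.

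Some stronger readings are tempting but unsupported:

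- **3.5 mmHg is the gap between PLHIV and uninfected people, so the plan assumes full normalisation.** A reader might infer this from how reference 23 is described, but no sentence says which groups gave the number. The citation follows the SD and may support only that figure.
- **Training must close such a gap in every participant.** The calculation concerns a difference in means, so only the average effect is assumed.
- **No training data exist at all.** The Introduction and Discussion cite training studies in other populations with favourable results. They are cited for direction, without a size of effect.
- **A null result would have to be called inconclusive unless its interval excludes half of some gap.** That is a preference about interpretation; nothing in the article makes it necessary.

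**Conclusion.** The point holds in a limited form: the basis cited for the planning figures does not match the contrast that the trial tests. This follows from the article's own text and does not depend on what reference 23 contains, which cannot be checked here.

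On the stated inputs, read as a two-sided two-sample t-test with 4.6 mmHg as the SD of the analysed change, the planned size gives 67% power for 3.5 mmHg with 21 per arm and 49% with 14 completers. The stated 80% is not met. If 4.6 mmHg is a single-visit SD, the difference detectable at 21 per arm runs from 4.8 to 3.2 mmHg over assumed correlations of 0.3 to 0.7. The documents do not support saying that the design cannot detect any partial effect: power at three quarters of 3.5 mmHg is 44% at 21 per arm with SD 4.6, which is low but not negligible.

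**What to change.** In the sample-size section:

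1. State which comparison and which measurement in reference 23 gave 3.5 and 4.6 mmHg. Present 3.5 mmHg as an assumed target for the mean group-by-time difference, not as a training effect supported by that reference.
2. Replace the 80% power statement with the detectable difference at the planned size and the assumed SD of change. With SD 4.6 this is 4.1 mmHg at 21 per arm and 5.1 mmHg at 14 completers. If 4.6 is a single-visit SD, give the range over the pre-post correlation (Step 3 of the working). Show power for smaller effects as well, such as 2.625 and 1.75 mmHg.
3. Commit to reporting the training effect with its confidence interval beside the baseline difference between PLHIV and the uninfected reference group (CONT), which the design already collects. The reader can then judge the size of the effect against the impairment seen in this trial.

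The cost is a few sentences. No participants, visits or measurements are added. The downside is that the stated power will probably look less favourable than 80%.
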